#### Economic analysis

The economic evaluation will consider the costs of personnel resources, supplies, and operating costs as described below. The analysis will not consider development of the PCOR-VIC database, as we consider that this cost will be identical regardless of the data collection modality. However, the additional costs associated with developing the automated email system within the register will be captured.Valuing personnel resourcesThe value of the research staff contacting patients will be measured in terms of salaries, allowances and benefits received during the study period for their time. At Monash University, all personnel maintain a time sheet for their usual activities. We shall calculate time taken for the data collection processes from time sheets for the period of data collection (February 2016-November 2016). As the level of competence required to undertake all tasks are comparable, we will cost the time using a consistent salary across all three groups.Valuing supplies and other recurrent costsThe values of line items outlined in Table 3 will be included as variable inputs and valued at the price at which they were obtained. Items obtained free of cost will be valued at market price – that is, the price paid if purchased from the local or international market. If price from the international market is used then that price will be changed in Australian dollars using the purchasing power parity (PPP) of Australian dollar with USD in 2015 [41]. The actual expenditure for rent, utilities and supervision during the year will be taken into account [41]. These costs data will be collected from the managers of the data collection facilities using a structured questionnaire.

**Table 3 Tab3:** Cost data collection of 3 different methods

	Telephone	Mail (Postal service)	E-mail
Personnel time cost (Time to contact and complete patient surveys, as well as administrative tasks such as filing forms, data entry, and checking patient data)	Spread sheet to keep the time of the data collection staff	Spread sheet to keep the time of the data collection staff	Spread sheet to keep the time of the data collection staff
Training cost (Time cost of the trainers and trainee, food costs if any and training materials costs)	Yes	Yes	Yes
Mail (envelope, stamp, mail cost) – printing	No	Yes	No
Email	No	No	No
Telephone costs – all receive initial phone call, plus telephone costs for collection via the telephone.	Yes	Yes	YesMethodology of time allocation of providersData collectors will maintain a spreadsheet to record the time spent for each data collection method. The time will be categorised into direct data collection and non-service professional activities which includes preparatory activities, maintaining and management of records and information, and obtaining supplies.
*Calculating Total and Average Costs:*
We will sum personnel costs, cost of supplies, training costs and costs of operation and maintenance to provide a total cost for each of the follow up methods as well as average cost for each constituent items.
*Estimating cost effectiveness*
To estimate the most cost-effective approach, incremental cost effectiveness ratios (ICERs) will be estimated. This involves comparing the incremental/additional cost of one approach with the additional outcome achieved by using that approach. Outcome will be measured as completed surveys. The most cost effective approach will be the method which achieves the greatest percentage of complete surveys at the least cost [42]. Scenario analysis will be undertaken to test some of the assumptions in estimating the cost of each approach.

### Cost projection modelling

A cost projection model will be developed based on the most cost-effective approach for collecting completed PROMs surveys. The model will use epidemiological data (Australian prostate cancer incidence data) and the estimated follow-up cost. A sensitivity analysis will be conducted using different follow up rates and cost assumptions.

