## Sample size

Sample size calculations were based on an equivalence study design [35] and the primary outcome measure (completeness of survey responses). Given the current follow up response rates from the PCOR-VIC we estimate that we will achieve a response rate of 90% [32] when PROMs are administered by the telephone follow-up method. The study was designed to evaluate whether the completeness of survey responses in the ‘mail/postal service group’ or ‘email group’ was similar to the ‘telephone’ group. Assuming that the equivalence margin is 10%, we will require 190 respondents per group. We have made an assumption that the 83% of who have internet access will also have an email account [36]. The sample size was adjusted accordingly so the final number of respondents required in each group is 229 giving a total number required n = 687 (Table 1). Our sample size has been calculated to provide a level of significance at 5% with 80% power (2-sided test). The sample size calculation was performed in Stata V13.0 [37].

**Table 1 Tab1:** Sample size calculation

Indicator	Targeted response rate	Equivalence margin	Sample size (SS) per group	Internet access	SS adjusted for email	Total Sample required
Response rate	90%	10%	190	83%	229	687

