4	To develop a model to determine the cost for national scale-up of PROMs data collection method with EPIC-26 survey in Australia.	A cost projection model will be developed based on most efficient approach. The model will use epidemiological data and estimated cost parameters. Estimated incidence data on national prostate cancer cases and completed follow up of patients will be forecasted. Using estimated cost data will help to determine the cost for national scale-up of follow up per year. A sensitivity analysis will be conducted with different assumptions e.g. (1) total number of prostate cancer patients; (2) completed follow up surveys and; (3) cost.
5	To provide recommendations for most cost-effective approach for complete follow-up of prostate cancer patient	A comprehensive report with recommendations will be developed.

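### The mode is chosen on trial-volume costs and only the winner is projected nationally, so the plan would not show whether the ranking changes at the scale the choice is for

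*Protocol article*

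**What the plan says.** All references are to the protocol article.

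- **Cost total.** In Economic analysis, the paragraph on total and average costs states: "We will sum personnel costs, cost of supplies, training costs and costs of operation and maintenance to provide a total cost" for each method, together with an average for each component. Earlier in the same section: "The actual expenditure for rent, utilities and supervision during the year will be taken into account". That section also says the extra cost of building the email system inside the register is captured.
- **Metric and choice.** Table 2, objective 3, defines cost-effectiveness as total cost divided by completed follow-ups. Economic analysis adds incremental ratios (ICERs) and calls most cost-effective the mode with the highest completion for the lowest cost.
- **Projection.** Table 2, objective 4: "A cost projection model will be developed based on most efficient approach". Cost projection modelling says the same: "A cost projection model will be developed based on the most cost-effective approach for collecting completed PROMs surveys".
- **Purpose.** The Discussion says that the cost of each completed survey will inform which mode is used when collection expands nationally. The steering committee and the funder make the decision.
- **Robustness checks.** The projection gets a sensitivity analysis over patient numbers, follow-up rates and cost. The trial costing gets a scenario analysis of some unspecified costing assumptions.

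**The concern.** A cost that is paid once weighs heavily when spread over 229 men and very little when spread over a national caseload. A per-man cost weighs the same at any volume. A mode that is dear to set up and cheap to run can therefore look worst in the trial and be cheapest at the volume for which it is being chosen.

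The plan ranks the modes first and projects second, and only the first-ranked mode is projected. No step separates fixed from per-man cost or compares the three modes at national volume. At stake is the choice of mode for national collection. The primary comparison of completion proportions is not affected.

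**Working it through.** **Inputs from the article (Sample size).** "Assuming that the equivalence margin is 10%, we will require 190 respondents per group"; "level of significance at 5% with 80% power (2-sided test"); an expected response of 90% by telephone; "We have made an assumption that the 83% of who have internet access will also have an email account".

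**Step 1: reproduce the trial volume.** For equivalence of two proportions, both 0.90, with margin 0.10, two one-sided tests at 0.025 and power 80% (beta/2 = 0.10), the normal quantiles are 1.960 and 1.282, which sum to 3.242:

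n = 2 × 0.90 × 0.10 × 3.242² / 0.10² = 189.2, rounded up to 190 per group.

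Then 190 / 0.83 = 228.9, rounded up to 229; 229 × 3 = 687. All three stated figures reproduce, so 229 is the volume over which each mode's trial cost is averaged.

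**Step 2: condition for a reversal.** Let one mode have a fixed cost higher by F and a per-man cost lower by s. At equal completion c, the cost per completed survey is (fixed + v × N) / (c × N), where v is the per-man cost. The high set-up mode is cheaper only when N > F/s. The trial and national rankings therefore differ when

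F / N_national < s < F / 229.

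**Step 3: illustration.** The article gives no cost amounts and no national volume. F, s, the unit costs and N_national = 10,000 are assumptions, in AUD.

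- F = 2,000: reversal for s between 0.20 and 8.73; break-even N is 1,000 at s = 2, then 400 at s = 5, then 200 at s = 10, then 100 at s = 20.
- F = 5,000: reversal for s between 0.50 and 21.83; break-even N is 2,500 at s = 2, then 1,000 at s = 5, then 500 at s = 10, then 250 at s = 20.
- F = 10,000: reversal for s between 1.00 and 43.67; break-even N is 5,000 at s = 2, then 2,000 at s = 5, then 1,000 at s = 10, then 500 at s = 20.
- F = 20,000: reversal for s between 2.00 and 87.34; break-even N is 10,000 at s = 2, then 4,000 at s = 5, then 2,000 at s = 10, then 1,000 at s = 20.

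In 14 of the 16 combinations the break-even exceeds 229, so the high set-up mode loses in the trial. In 13 of those 14 it is cheaper at 10,000 men; the other (F = 20,000, s = 2) is a tie. These counts describe the assumed grid and are not a probability.

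**Step 4: worked example.** Assume AUD 25 per man with no set-up for telephone, and AUD 15 per man plus a set-up of AUD 5,000 for email. Completion is 90% in both. The cost per man is the set-up divided by N plus the variable cost; dividing by 0.90 gives the cost per completed survey.

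- N = 229: AUD 27.78 for telephone (from 25 divided by 0.90) and AUD 40.93 for email (total cost AUD 8,435, divided by 0.90 × 229). Telephone is cheaper.
- N = 10,000: AUD 27.78 for telephone and AUD 17.22 for email (total cost AUD 155,000, divided by 9,000 completed surveys). Email is cheaper.

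**Step 5: unequal completion.** Suppose email completion is 85%. At 229 men, telephone costs in total AUD 5,725 against AUD 8,435 for email, a difference of AUD −2,710, and gains 0.05 × 229 = 11.45 completed surveys. The ICER of telephone over email is AUD −236.68: telephone is cheaper and more complete, so it dominates. At 10,000 men, telephone costs in total AUD 250,000 against AUD 155,000 for email, a difference of AUD 95,000, and gains 500 completed surveys. The ICER is AUD 190 per extra completed survey, so there is a trade-off to weigh. The ICER, too, depends on volume.

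**The case against.** The strongest reply is that the mechanism needs a fixed cost that both differs between modes and enters the total, and the article does not clearly show one. The summed heads are personnel, supplies, training, and operation and maintenance. Email development is not named among them, and the first secondary objective concerns recurrent costs. Table 3 marks training for all three modes. Rent, utilities and supervision are facility costs with no stated difference by mode, and some may grow with volume. This stands, and it makes the point conditional. It does not remove it, because Economic analysis says the email development cost is captured without saying whether it enters the ratio.

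A second reply is that scale is already considered. Trial design says that activity-based costing helps show the composition of costs and what wider coverage would cost. Component averages are planned, and the scenario analysis covers each approach. This stands in part: most of the data for the fix will exist. But the scenario analysis does not name scale, and the sensitivity analysis belongs to a projection built on the chosen mode, so neither ensures a comparison of modes at national volume.

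A third reply is that the size is assumed. That is correct. With a saving of AUD 20 per man, any F below 20 × 229 = AUD 4,580 gives no reversal. Every arm receives the initial call, and non-responders to mail and email are telephoned, so the true per-man gap may be smaller than the illustrations. A smaller gap raises the break-even volume, so this does not settle the direction.

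Finally, the committee and the funder weigh cost against completeness, so the ranking does not bind them. Under the plan as written, however, they would see a national projection for one mode only.

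**Conclusion.** The point holds in conditional form. The order of steps allows a mode with higher set-up and lower running cost to be set aside before national volume is examined, and no stated analysis ensures that this would be noticed. A reversal requires a fixed-cost gap F in the total and a per-man saving between F/N_national and F/229, at equal completion. Its size cannot be determined from the documents; the AUD 0.50 to 21.83 range rests on an assumed F of AUD 5,000 and 10,000 men.

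A reader might infer two stronger claims, and neither is supported. The first is that the national ranking does differ from the trial ranking. Without cost amounts, one can say only that it need not be the same. The second is that the plan must overstate the national budget by multiplying a trial average, one-off costs included, by national volume. The article says only that the model uses incidence data and the estimated follow-up cost; it does not state linear scaling of that average.

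This is a low-cost improvement that bears directly on the scale-up question, not a defect in the trial's primary analysis.

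**What to change.** 1. In Economic analysis, report each mode's cost in two parts: a fixed part and a variable part per randomised man. State whether email-system development is in the fixed part and, for training and overheads, which items are shared and which are specific to a mode.
2. In Table 2 (objective 4) and Cost projection modelling, run the national projection for all three modes as: fixed cost × number of times it is incurred nationally + variable cost × men due for 12-month follow-up. Give projected completed surveys for each mode alongside. The multiplier handles costs that recur with expansion and one-off work that can be reused.
3. Apply the planned sensitivity analysis to all three projections, and name the mode for scale-up from them. Keep the trial-scale ICERs as the within-trial result.

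**Cost:** a fixed/variable classification of items already being collected and two further runs of the same model. No new data collection is needed, and randomisation, sample size and the primary analysis do not change.

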## Quality assurance

This study will be conducted in accordance with the National Health and Medical Research Council (NHMRC) Code of Responsible Conduct of Research.

## Dissemination of results and publication policy

Results of this study will be disseminated to the scientific community through conferences, seminars presentations and publications in peer-reviewed journals. We will present the findings at the Registry Special Interest Group at Monash University to ensure that the lessons learned in the PCOR-VIC registry are made available to other registry custodians.

## Data storage, access and security arrangements

The PCOR-VIC data are housed on a secure server at Monash University. Security is maintained using encryption of data, a managed and audited protocol for access, training and accreditation of personnel, role-based access and authentication of data. The database storing PROMs and costing data will be password protected and stored on a networked server that is backed up on a daily basis at Monash University.

## Potential risks

As the participants are diagnosed with prostate cancer, they may experience distress when discussing the disease with follow up staff over telephone. There will be no pressure on the participants to divulge any information if they do not feel comfortable to do so. An offer will be made to terminate the interview if the participants exhibit any signs of distress. The interview will only be continued if the participants want to do so. As there will be no physical examination, biomedical tests (invasive/non-invasive) or use of hazardous material, this project is deemed to be a low-risk research activity.

## Discussion

Through this economic analysis we will determine the most cost-effective means of capturing PROMs and completing follow up of prostate cancer patients through the PCOR-VIC using the EPIC-26 survey. Our primary aim therefore is to identify the value of different PROMS collection methods. Value is defined as outcomes relative to costs and encompasses efficiency [43]. The outcome we will be evaluating is response rates and representativeness of the various tools in assessing the quality of life. With knowledge of the cost of each completed survey, we will decide which approach to use as we expand data collection to obtain national coverage. Our primary objective is to assess the response rate across each data collection approach. Surveys will only be considered as completed if all relevant questions have been answered.

This will provide guidance to other registries undertaking follow up surveys of patients and it will also allow us to estimate the cost for collecting PROMs data within the Prostate Cancer Outcome Registry- Australia. Moreover we will be able to understand the quality of PROMs data collected by the three different methods. It may be that one method produces significantly higher rate of missing data or questions which patients decline to answer. We have to weigh the cost of data collection against completeness of surveys to determine the method which provides the greatest value at the end of the study. This decision will be made by the project steering committee and the funder.

## Conclusion

The aim of this study is to provide evidence on which method of PROMs follow up data collection is more cost-effective. Findings of this study will also help us in understanding the cost for national implementation of the prostate cancer quality of life questionnaire in Australia.

## Abbreviations

ABC: Activity Based Costing
EPIC-26: Expanded Prostate Cancer Index Composite
GP: General Practitioner
ICERs: Incremental Cost Effectiveness Ratios
ITT: Intention to Treat
MGS: Monash Graduate Scholarship
MIPRS: Monash International Postgraduate Research Fellowship
NHMRC: National Health and Medical Research Council
PCa: Prostate Cancer
PCOR-VIC: Prostate Cancer Outcome Registry- Victoria
PPP: Purchasing Power Parity
PROMs: Patient Reported Outcome Measures
PSA: Prostate Specific Antigen
RCT: Randomized Controlled Trial
TURP: Transurethral Resection of The Prostate
URL: Uniform Resource Locator
